### 2.4. Intervention Group

After being divided, the participants will be allocated into one of the two study groups: either the control group (CG) or the Multicomponent Aquatic Training program group (MAT group).

The project team will be comprised of physical therapists (experienced in both aquatic physical therapy and PD) and physical therapy students. The physical training will be offered free of charge to the participants, who will be asked not to start any other type of physical training during the study.

### 2.5. Multicomponent Aquatic Training (MAT)

The MAT was developed with PD patients classified between stages 1 to 4 in HY scale as the target population. The individuals allocated to the MAT group will be enrolled in a 12-week program with two 50-min sessions per week with at least 72 h between sessions, totaling 24 sessions.

The activities will take place in the pool at the Ana Carolina Moura Xavier Rehabilitation Hospital Center, in Curitiba, Paraná, Brazil. Due to the size and depth of the pool (10.75 m × 2.90 m; and 1.10 m deep), the groups will be limited to no more than six participants at a time. The pool will be kept at a mean temperature of 33 degrees Celsius.

Despite training being carried out in groups, there will be an experienced physical therapist and three physical therapy students in the pool to assist and instruct the patients while performing the exercises. Hence, individual attention will be provided, minimizing the risk of incidents in the water. There will also be another two physical therapy students outside the pool to provide support. These professionals will also record the arterial pressure (AP) and heart rate (HR) before and after the training, also being available in case any participant requires help during the intervention.

All training sessions will be separated as follows: functional mobility training and adjustment to the water (about 10 min); strength and muscle power exercises (about 10 min); balance or neuromotor exercises (about 20 min); and relaxation/cooldown (about 10 min). The MAT is described in detail in Annex 1, organized according to Israel’s five phases for learning aquatic motor skills [19], namely: (1) description of the activity, (2) main physical and thermal properties of the water involving the immersed body, (3) parameters of exercise progression, (4) transference of skills to land, and (5) classification of mobility in the ICF domains of activities and participation.

The training will be approached by progressively increasing volume and intensity to stimulate the participants’ neuroplastic potential [20]. Accordingly, every 4 weeks, training will be adjusted, with an increase in the degree of difficulty and complexity of the exercises. Table 1 describes the order and organization of the activities per week and intervention varieties, specifying which mobility/adjustment, muscle strength, balance, and relaxation training should be used.

### 2.6. Control Group

The participants allocated to the control group will be instructed not to change their usual activities throughout the study. Once the experimental period is completed, the intervention will be offered to the control participants free of charge.

### 2.7. Adverse Results

Adverse events will be monitored and prevented as the participants will be accompanied during their transition to the pool, throughout the exercise, and when their HR and AP are measured, always monitoring the intensity of their effort during the physical activity. During aquatic physical training, the participants will be individually accompanied by physical therapists and/or a support team inside and outside of the pool to ensure they do not perform the exercises incorrectly, thus avoiding aquatic accidents, such as momentary drownings.

In addition, the professionals will record the AP, HR, and breathing rate of participants before and after the training. In the event of any falls or incidents related to the subjects’ health status occurring during the intervention, the events will be recorded accordingly. During the training, the participants will also be monitored with the perceived exertion scale (BORG C20) to ensure they do not exceed the recommended intensity level. Participants must remain between 13 and 17, which would correspond to 66% and 80% of maximum voluntary strength production, respectively, as recommended by the American College of Sports Medicine 2014 [11]. If any musculoskeletal injuries occur, the training will be halted.

If any of the participants interrupt the protocol, follow-up data will be collected, and the adverse effects will be reported in the publication of the results. Delayed onset muscle soreness following physical training will not be considered an adverse effect as it is an expected result of the exercise. In the event of muscle soreness, participants will be referred for cryotherapy.

### 2.8. Recruitment

The participants will be informed about the project via a phone call and then invited to participate in the initial assessment. Before beginning the assessment, they will be informed of their voluntary participation in the study and sign the informed consent form—which has been revised and approved by the Ethics Committee of the Department of Health Sciences at the Federal University of Paraná. The study will be conducted in compliance with Brazilian Resolution 466/12, which is in line with the World Medical Association Declaration of Helsinki.

Other assessments planned for the pre-intervention period will be scheduled for the participants who meet the inclusion criteria and do not meet any of the exclusion criteria, as schematized in Figure 1.

The research team will read the informed consent form together with the participant and answer any questions they might have. Once the participants are fully informed and feel sure on their participation, they will sign two copies of the document (researchers and participants). All the collected data will be stored in secure locations, identified only with the participants’ code. The data will be used for publication in scientific journals without identifying any of the participants. In addition, at the end of the study, the participants will be handed a report with the data of their initial and final assessments. The data will be published regardless of the effects of the intervention—i.e., whether they are positive or negative.

### 2.9. Separation of the Groups and Allocation Concealment

The allocation of the 2 groups will be based on patient preference. Before completing the pre-intervention assessments, the participants will be divided into two equal-sized groups. The researcher responsible for the assessment will not know which group each participant is allocated to.

The participants will be instructed not to tell the researchers who assess them which study group they are a part of. Thus, the researchers who conduct the assessments will be blinded to the allocation and size of the groups.

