### 2.14. Sample Size

A sample size calculation was used to determine the number of participants required for the present study. The calculation was based on the prevalence of PD in Curitiba, Paraná. The sample calculation was performed using GPower 3.1 software, which stipulated a minimum sample of 30 individuals, assuming an effect size of 0.25 on a probability distribution F, whose value consisted of a mean distance between the sample mean and the population mean; a Type I error equal to 0.05 and analysis power equal to 0.84. Thus, the study will require 30 individuals with PD—15 allocated in the MAT group, and 15 in the control group. However, an extra 10% of participants will be added in order to avoid possible drop outs.

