The warm-up exercises are related to functional mobility and adaptation to the aquatic environment. Most include regular functional movements, such as walking in different directions, spinning, jumping, running, squatting, and diving to control breathing. Due to inherent trunk stiffness in those with PD, there will be axial exercises with spinning in all sessions.

The main training has exercises to develop lower limb muscle strength and power, as well as balance. Kicking and leg abduction/adduction were chosen as they activate large muscle groups, and also demand single foot support while the opposite limb combats hydrodynamic properties. Exercise progression was designed to be both quantity and load-based, respecting individual tolerance, as the participants will have different disability levels.

The balance training will include negotiating obstacles, changing postures, fluctuating postural control, using floating devices to increase instability during upright movements. The aquatic environment destabilizes the immersed body, stimulating postural control adjustments while reducing risks in case of falls [35]. The progression was based on the quality of movement and the decrease in upper limb support.

Finally, to relax and cool down, Ai-Chi sequences will be used. Respiratory control associated with big ranges of motion allows for simultaneous relaxation and stretching [36].

The aquatic environment is important for developing motor skills, and can be used as a resource for learning at different levels of physical disability. In populations such as PD, this learning should transfer to land. This would eventually increase the motor skillset when facing activities of daily living [35]. For this transfer of skillsets, Appendix A presents the expected conditions related to the main motor symptoms of PD, and also the International Classification of Functioning domains. The target is to extend the learning obtained from the aquatic environment through an increase in social participation of persons with PD. 

Lastly, this intervention protocol was developed to test a clinical intervention in this population, complying with the methodological recommendations necessary to obtain high quality results [23].

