This clinical trial may have the following limitations: (1) difficulty recruiting individuals and having them adhere to a 12-week study plus the pre- and post-intervention assessment period; (2) the inability of some participants getting to the center where data collection will be made, especially those with stage four PD; (3) the MAT proposed may not be enough to cause favorable changes in all the stages of the disease, due to variability in participant characteristics and disease progress.

Furthermore, the protocol does not include: (1) the analysis of neuromuscular parameters (such as electromyography and reaction time) to understand the mechanisms involved in gaining muscle mass and strength; (2) the use of individual waterproof heart monitors during the intervention (aquatic heart rate meters, for instance) to follow up the heart rate oscillations. All these limitations must be considered in further research.

If the MAT provides positive results in terms of controlling the progress of PD symptoms with the parameters assessed, similar studies may be conducted to assist this population. Furthermore, as the protocol is described in detail, it can be used in public health and clinical practice, helping professionals and patients handle the symptoms and slow the progress of the disease.

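### Participants choose their own group and the stated analysis names no adjustment, so a difference in change between groups cannot be attributed to the aquatic training alone

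*Protocol article*

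**What the plan says.** All references are to the protocol article.

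- **Allocation (2.9).** "The allocation of the 2 groups will be based on patient preference". The next sentence says that "the participants will be divided into two equal-sized groups". The section title promises allocation concealment, but the text under it describes only keeping assessors unaware of group membership.
- **Group sizes (2.14).** "15 allocated in the MAT group, and 15 in the control group", plus 10% for dropout.
- **Aim (3, Discussion).** The study is to develop the training programme and determine its effects on muscle function, balance and mobility.
- **Analysis (2.15).** A mixed-model ANOVA compares initial with final assessment and one group with the other. No covariate is named.
- **What each arm does (2.5, 2.6).** The training group attends 24 pool sessions over 12 weeks. Controls keep to their usual activities, and after the experimental period "the intervention will be offered to the control participants free of charge".
- **Limitations (3, Discussion).** Recruitment, adherence, travel and variable response are listed. Self-selection is not. The Discussion nevertheless describes the protocol as "complying with the methodological recommendations necessary to obtain high quality results".
- **Design label (Abstract, 2.1).** Single-blind and controlled. The word randomised is not used.

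**The concern.** The aim is causal, but the groups are formed by the participants themselves. People who volunteer for two pool sessions a week for 12 weeks may differ from those who decline in disease stage, motivation or ease of travel. Section 2.11 says that the primary outcomes are directly affected by disease progression, so an imbalance in stage can act on the change over three months as well as on the starting level. The group-by-time term would then mix the effect of the training with the effect of who chose it.

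A larger sample would not help: it narrows the interval around a biased estimate. The instruction to form equal groups adds a practical gap, since nothing says what happens when choices are uneven.

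**Working it through.** **1. The plan's own figure.** Section 2.14 gives N = 30, "assuming an effect size of 0.25 on a probability distribution F", and "a Type I error equal to 0.05 and analysis power equal to 0.84". For a group-by-time interaction with 2 groups and m = 2 assessments, the noncentrality is λ = f²·N·m/(1−ρ) on F(1, 28), where ρ is the pre/post correlation. The article does not state ρ.

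- ρ = 0.5: λ = 0.0625 × 30 × 2 / 0.5 = 7.5, power 0.753.
- ρ = 0.6: λ = 3.75 / 0.4 = 9.375, power 0.840.

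The stated power is therefore reached with two assessments if ρ is about 0.6. It is also reached with three assessments and ρ = 0.5 (0.841), but the design has two. The point made here does not depend on which was used. The calculation only suggests a plausible range for ρ, taken below as 0.5 to 0.7.

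**2. What the pre/post comparison removes.** Write the outcome of person i as a level plus a change. If choosers of the training start at a different level but change at the same rate, the difference cancels in the group-by-time term. If they change at a different rate, by an average of b outcome SD, that amount stays in the term and is added to any effect of training.

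**3. Illustration of size.** Suppose the training has no effect and selection alone produces a difference in mean change of b, in units of the outcome SD. The variance of a change score is 2(1−ρ) outcome variances. With 15 per arm, λ = [b²/(2(1−ρ))] × (15/2) = 15b²/(4(1−ρ)). The test rejects when F(1, 28) exceeds 4.196. Both b and ρ are assumptions; the article supplies neither.

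| b (outcome SD) | ρ | λ | Rejection rate |
|---|---|---|---|
| 0.3 | 0.5 | 0.675 | 12.5% |
| 0.3 | 0.6 | 0.844 | 14.4% |
| 0.3 | 0.7 | 1.125 | 17.6% |
| 0.5 | 0.5 | 1.875 | 26.2% |
| 0.5 | 0.6 | 2.344 | 31.5% |
| 0.5 | 0.7 | 3.125 | 40.0% |

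The nominal rate is 5%. For scale, setting 15b²/(4(1−ρ)) equal to the planned 3.75/(1−ρ) gives b = 1, so on this reading of f the two assumed shifts are 30% and 50% of the effect the trial is sized to detect.

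**4. Equal groups from free choice.** If exactly 30 people chose freely, with an assumed probability p of choosing the training, the chance of a 15:15 split is 14.4% at p = 0.5, 7.8% at 0.6 and 1.1% at 0.7. With 33 recruited (30 × 1.10), the chance of at least 15 in each group is 51%, 29% and 4%. These figures assume a fixed total and no quota. They show only that a rule is needed, and none is given.

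**The case against.** Several objections deserve weight.

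- **The trial never claims to be randomised.** This is correct. The allocation method is stated openly, so no false label is alleged. The difficulty is that the method does not support the causal aim in the Discussion.
- **Preference and equal groups can coexist.** This also stands. Recruiting until 15 people have chosen each arm would satisfy both sentences, and section 2.6's delayed offer of training might help to fill the control arm. A reader might infer that the two sentences are incompatible, or that someone must be placed against their wish. The text supports only that the reconciling rule is unstated.
- **The direction of bias is unknown.** A reader might infer from the limitation about "the inability of some participants getting to the center where data collection will be made, especially those with stage four PD" that less mobile patients will choose control. That sentence concerns reaching the data-collection centre, which both arms must do, and section 2.3 requires everyone to walk unassisted. The 24 pool visits required of one arm only make selection on access plausible, but more impaired patients might equally prefer treatment.
- **Expectation effects would remain under randomisation.** True: participants know whether they are in the pool under either method. Expectation is therefore not part of this point.
- **An analysis plan that is not shown may add covariates.** It may. Covariates can adjust for measured factors such as stage. They cannot adjust for unmeasured motivation, and they do not change the allocation method stated here.
- **The main objective is to develop the programme.** The Abstract and Introduction say so, but the Discussion adds determining its effects, and the trial is sized and tested for that.

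**Conclusion.** The point holds. Allocation by preference, combined with a group-by-time comparison for which no adjustment is named, leaves the between-group difference in change open to confounding that the pre/post design does not remove. The limitations do not mention it.

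Its size cannot be derived from the article. The rejection rates of 12–18% for a 0.3 SD shift and 26–40% for a 0.5 SD shift are illustrations. They rest on an assumed shift, an assumed correlation of 0.5 to 0.7, no true effect and 15 per arm.

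Two lesser defects in section 2.9 also stand: there is no rule for reaching equal groups, and the title announces allocation concealment where the text gives assessor blinding. A reader might go further and conclude that the trial can say nothing about the training. The documents do not support that: a controlled non-randomised comparison gives weaker evidence, not none.

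**What to change.** **Preferred.** Replace preference in section 2.9 with a concealed, computer-generated 1:1 list in blocks, stratified by Hoehn and Yahr stage (1–2 versus 3–4). Release each assignment only after baseline is complete. Section 2.1 already places baseline before division into groups; section 2.9, which divides participants before those assessments are finished, should be brought into line. The sample size stays at 30 plus the dropout allowance. Because controls are offered the training afterwards, nobody loses access. The cost is an ethics and registry amendment, preparation of the list, and possibly a few refusals from people with a firm preference.

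**If preference is kept:**

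1. State how equal groups are reached, for example by a recruitment quota per arm.
2. Retitle section 2.9 as assessor blinding.
3. Describe the trial explicitly as non-randomised.
4. Adjust the group comparison of change for Hoehn and Yahr stage and age. Run a model adjusted for the baseline value as a sensitivity analysis, since change-score and baseline-adjusted analyses can disagree when self-selected groups differ at the start.
5. Add self-selection to the limitations.
6. Limit the conclusion to an adjusted association.

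This fallback costs little beyond wording and covariates: stage and the outcome baselines are already collected (section 2.10). It does not remove confounding by unmeasured factors such as motivation.

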## 2. Method

### 2.1. Study Design

This is a protocol for a single blind controlled clinical trial with two parallel groups, into which the participants will be allocated.

The MAT study protocol was developed based on the Standard Protocol Items: Recommendations for Interventional Trials (SPIRIT) [17]. The project was approved by the Ethics Committee of the Department of Health Sciences at the Federal University of Paraná, Curitiba, Paraná, Brazil (CAAE no. 66781417.4.0000.0102 and certification no. 2.200.372), and filed in the Brazilian Registry of Clinical Trials under RBR-6hnqcv. This is a Multicomponent Aquatic Training program, named MAT, to be conducted with participants with a clinical diagnosis of PD. The enrolled PD patients will be assessed at baseline (i.e., before dividing them into groups) and after three months. Any changes made in the protocol will be reported to the Research Ethics Committee and changed in the Brazilian Registry of Clinical Trials.

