### 2.10. Assessment

All assessments will be conducted before and after the intervention. A clinical assessment will be also conducted to classify the disease staging with the HY scale, which will be used only at the beginning due to its classificatory nature. Due to the amount of tests and measures, and to prevent participant fatigue, the assessments will be over 2 days.

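### Sections 2.1 and 2.9 put baseline and group formation in opposite orders, so part of an effort-dependent baseline may be measured after participants know their group

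*Protocol article*

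**What the plan says.** Section 2.1 (Study Design): "The enrolled PD patients will be assessed at baseline (i.e., before dividing them into groups) and after three months".

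Section 2.9 (Separation of the Groups and Allocation Concealment): "Before completing the pre-intervention assessments, the participants will be divided into two equal-sized groups". The sentence before it gives the method of division: "The allocation of the 2 groups will be based on patient preference".

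On blinding, section 2.1 calls the trial single blind. Section 2.9 adds "The researcher responsible for the assessment will not know which group each participant is allocated to" and "The participants will be instructed not to tell the researchers who assess them which study group they are a part of". Participants therefore know their group once it is formed, and the blinding covers the assessors.

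Section 2.10 spreads the testing out: "to prevent participant fatigue, the assessments will be over 2 days". Section 2.8 also stages it, with an initial assessment first and the remaining pre-intervention assessments scheduled afterwards for those found eligible. It refers to Figure 1, which is not reproduced in the text available.

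Section 2.15 analyses initial and final values between groups with a mixed-model ANOVA.

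**The concern.** In a pre-post comparison the baseline has to be free of any influence from the group a person is in. Several of the measures here depend on how hard a participant tries, what pace they choose or how they rate themselves: isokinetic strength, the Five-Times-Sit-to-Stand, TUG and gait speed at a self-chosen pace (section 2.11), and the PDQ-39 (section 2.12). Someone who already knows that they will, or will not, receive the aquatic training may perform or answer differently.

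Assessor blinding guards against bias in how the assessor scores. It has no hold on the participant's effort or self-report. If the section 2.9 order is used, the instruction not to reveal the group also has to work from baseline onward instead of only at follow-up.

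The stake is the group-by-time effect on the primary outcomes. A baseline difference produced by knowing the group is subtracted from the final score and appears as a difference in change. Baseline data collected in this way cannot be collected again once training has started.

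**Working it through.** **Step 1: the two statements side by side.**

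| Place | Order stated |
|---|---|
| Section 2.1 | Baseline first, then division into groups |
| Section 2.9 | Division into groups, with pre-intervention assessment not yet complete |

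Under section 2.1 no baseline test follows division. Under section 2.9 at least one does.

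**Step 2: can they be reconciled?** Baseline in section 2.1 could be read as only the initial assessment of section 2.8, with groups formed before the later pre-intervention tests. The text does not say so, and outcome tests would then still follow group formation. Alternatively, section 2.9 may be a slip for *after completing*. In that case the sentence is wrong and needs correcting. Figure 1 might show the intended order, but the two sentences would still disagree.

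**Step 3: how a baseline shift reaches the test.** With two time points, the group-by-time test in the mixed ANOVA is the comparison of mean change scores. Let the outcome SD be 1 at each visit, the pre-post correlation ρ, and n participants per group.

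- Variance of one change score: 2(1−ρ)
- Variance of the difference in mean change: 2 × 2(1−ρ)/n = 4(1−ρ)/n
- With a baseline shift of s SD in one group, no true effect and follow-up scores unaffected, the expected difference in change is s in absolute value
- Noncentrality: λ = s²·n/(4(1−ρ)), on F with 1 and 2n−2 degrees of freedom

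**Step 4: inputs.** n = 15 per group and type I error 0.05 come from section 2.14, giving F(1, 28) with a critical value of 4.196. Both s and ρ are assumptions, because the document gives neither.

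The size of ρ has one indirect check. Section 2.14 states f = 0.25, N = 30 and power 0.84. For the interaction, λ = f²·N·2/(1−ρ). With ρ = 0.6 this is 0.0625 × 30 × 2/0.4 = 9.375 and power is 0.840. With ρ = 0.5 it is 7.5 and power is 0.753. So 0.6 is consistent with the stated power if the calculation was for the interaction, but the article does not report it.

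**Step 5: results.** Worked example with s = 0.2 and ρ = 0.6: λ = 0.04 × 15/(4 × 0.4) = 0.375, and the false-positive rate is 9.1%.

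| Baseline shift in one group | ρ = 0.3 | ρ = 0.5 | ρ = 0.6 | ρ = 0.8 |
|---|---|---|---|---|
| 0.1 SD | 5.6% | 5.8% | 6.0% | 7.0% |
| 0.2 SD | 7.3% | 8.3% | 9.1% | 13.3% |
| 0.3 SD | 10.3% | 12.5% | 14.4% | 24.1% |

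The nominal rate is 5%. A small shift does little. A shift of 0.3 SD at least doubles the rate across this range.

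**The case against.** The strongest objection is that allocation is by patient preference. Participants may know which group they want, and expect to get it, before any formal division. Postponing the division alone would then not give a baseline taken without that expectation. This stands, and it changes the remedy: the preference itself must be elicited after baseline. It also means that confounding by preference is present under either order and probably outweighs this point.

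Second, the figures rest on assumed shifts and an assumed correlation, and they hold follow-up scores fixed. Participants certainly know their group at follow-up, so an effort effect there could offset a baseline shift or add to it. This also stands, so the table is an illustration and not an estimate.

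Third, a reader might infer that the entire baseline is taken with knowledge of the group, or that people will drop out selectively by group before baseline ends. The documents support neither. Section 2.9 says only that division precedes completion, section 2.8 describes staged assessment, and nothing in the text bears on early drop-out by group. Which outcome tests would follow division is unknown.

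What the objection does not remove is the contradiction. The article fixes the order twice and the two statements disagree. This is not detail that an article would leave to a fuller document.

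**Conclusion.** The inconsistency is real and should be corrected. As written, sections 2.1 and 2.9 cannot both apply to the full two-day baseline. If section 2.9 governs, at least part of the baseline is exposed to knowledge of the group, and the planned analysis carries any resulting shift into the group-by-time contrast without protection from assessor blinding.

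The size and direction of the bias cannot be derived from the document. Under the assumptions listed in the working, the false-positive rate ranges from barely above nominal to about 24%. It would be tempting to quote a single pair of values from that table as the effect on this trial, but the document supplies neither the shift nor the correlation that this would need.

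Severity is moderate. The flaw is avoidable and adds to the larger, separate problem of preference-based allocation, but it is not the main threat to the comparison.

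**What to change.** Keep the order in section 2.1 and replace the conflicting sentence in section 2.9 with:

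> Both baseline assessment days are completed and recorded before the participant's group preference is elicited and before groups are formed or disclosed.

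Check Figure 1 against this order and change it if it differs.

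The cost is one sentence and a scheduling step, with no added visits or staff. The change does not address confounding by preference, and at follow-up the blinding still depends on participants not revealing their group.
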